#### Medical visit

After the intervention visit, the patient will bring the list of questions into their regularly scheduled medical visit. With permission of the patient and the physician, the visit will be audio recorded using a portable digital recorder that the coach will place in the examination room and collect after the visit. Before beginning the recording, the coach will remind the patient that recording the visit is optional. If either the patient or the physician prefers that the visit not be recorded, the coach will not record the visit. In cases where the recording was not done, the study endpoints that require audio recordings will not be evaluated for that patient, but the remaining endpoints will be evaluated from the other data sources. No members of the study team will attend the medical visit, but will wait until after the visit to collect the recorder.

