#### Study enrollment

Interested prospective participants will meet with the study coach in a private area in the clinic to discuss the study and, if interested, sign a consent form and HIPAA authorization form. Once informed consent is granted, the participant will be asked to complete a brief baseline survey, available in English or Spanish, with questions about sociodemographic characteristics, barriers to disease management and medication adherence. Participants will be assured that they can opt not to respond to any of the questions. The coach can read questions to any participants having difficulty reading the survey.

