#### Sample size

The target sample size is 190 (95 participants per group) to allow us to detect a 50% difference in the rate of occurrence of the primary outcome between the intervention and comparison group with 80% power and an alpha = 0.05. This assumes we observe a base rate of the outcome of 40% in the active comparator group, as we have observed in an unpublished analysis of data from a prior study, and 60% in the EMPATHy + Coached Care intervention group.

The sample size calculations do not account for loss to follow-up because the first primary outcome (development of a contextualized plan of care) is collected at the single intervention visit, and the second primary outcome (attainment of a concrete behavioral goal) is collected via telephone after a fairly short follow-up period (2 weeks) in patients who regularly access the clinic. Results from this pilot study will be used to estimate the rate of loss to follow-up for a definitive effectiveness trial.

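### The final decision to record the visit comes after the allocated coaching, and no decision before allocation is shown, so missing first primary outcomes could differ by arm

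*Protocol article*

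**What the plan says.** The order of events can be read from the Study procedures sections of the protocol article.

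- **Study enrollment:** interested patients meet the study coach, "sign a consent form and HIPAA authorization form", and then complete the baseline survey. The section does not mention a recording decision.
- **Pre-visit coaching session:** the arm-specific content is delivered here, as the tablet activity in one arm and an unstructured discussion in the other. Patients in both arms leave with one to three questions for the physician.
- **Medical visit:** this follows the coaching. Recording needs the permission of patient and physician, and either can prevent it. On the patient's side: "Before beginning the recording, the coach will remind the patient that recording the visit is optional". On the consequence: "In cases where the recording was not done, the study endpoints that require audio recordings will not be evaluated for that patient".
- **Outcome assessments:** the recording is the only source for the first primary outcome (contextualized plan of care) and the first secondary outcome (discussion of a contextual factor).
- **Study procedures, opening paragraph:** both study coaches deliver both versions, so the coach who gives the reminder knows the allocation.
- **Sample size:** "The sample size calculations do not account for loss to follow-up". The reason given for the first primary outcome is that it is obtained at the single intervention visit. Unrecorded visits are not mentioned.

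**The concern.** Whether a patient has a first primary outcome at all is settled after the patient has received the allocated coaching. What the patient is about to say on tape is what the intervention is meant to change and what the endpoint scores. If the coaching, or the way an unblinded coach words the reminder, alters willingness to be recorded, the recorded patients in the two arms are no longer comparable groups formed by randomization. The physician's permission adds a second route, and the article gives it no stated timing relative to allocation.

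At stake is the validity of the comparison on one of two primary outcomes. This is separate from the loss of power when visits go unrecorded: recruiting more patients would restore power but would not remove selection.

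**Working it through.** **1. The plan's own figure.** The inputs, all from Sample size, are "This assumes we observe a base rate of the outcome of 40% in the active comparator group", "60% in the EMPATHy + Coached Care intervention group", and "with 80% power and an alpha = 0.05" (sidedness is not stated; two-sided is assumed). With unpooled variance, n per arm = (1.960 + 0.842)² × (0.24 + 0.24) / 0.20² = 94.2, so 95 per arm. This matches "The target sample size is 190 (95 participants per group"). With pooled variance the result is 97 per arm, and the power at 95 per arm is 79.2%. The planned size is sound for complete data, and this point does not alter it.

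**2. Bias from unequal refusal, with no true effect.** Assume a true rate of 40% in both arms. Let m be the share of visits not recorded and r the success rate among them. The rate seen among recorded visits is (0.40 − m·r) / (1 − m). Both m and r are assumptions. The false difference below is the arm with more refusals minus the other arm.

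| Refusal | r | Arm with more refusals | Other arm | False difference |
|---|---|---|---|---|
| 20% v 10% | 0.10 | 0.380/0.80 = 0.475 | 0.390/0.90 = 0.433 | +4.2 points |
| 20% v 10% | 0.20 | 0.360/0.80 = 0.450 | 0.380/0.90 = 0.422 | +2.8 |
| 20% v 10% | 0.40 | 0.320/0.80 = 0.400 | 0.360/0.90 = 0.400 | 0 |
| 20% v 10% | 0.60 | 0.280/0.80 = 0.350 | 0.340/0.90 = 0.378 | −2.8 |
| 30% v 10% | 0.10 | 0.370/0.70 = 0.529 | 0.390/0.90 = 0.433 | +9.5 |
| 30% v 10% | 0.60 | 0.220/0.70 = 0.314 | 0.340/0.90 = 0.378 | −6.3 |
| 5% v 3% | 0.10 | 0.395/0.95 = 0.416 | 0.397/0.97 = 0.409 | +0.7 |

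The sign depends on whether refusers would have done worse or better than average. The size depends on the gap in refusal.

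**3. Similar refusal totals do not exclude bias.** Again take 40% in both arms, with 90% of control visits recorded regardless of outcome. Suppose EMPATHy visits that would yield a plan are recorded 95% of the time and the others 85%.

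- Share recorded in the EMPATHy arm: 0.40 × 0.95 + 0.60 × 0.85 = 0.89, close to the control arm's 0.90.
- Observed EMPATHy rate: 0.38 / 0.89 = 42.7%, a bias of +2.7 points.
- The two-sided type I error is then about 6.5%. At 95%/80% the bias is +4.2 points (type I error 8.5%), and at 95%/70% it is +7.5 points (16%).
- If recording is unrelated to outcome, the bias is 0 and the type I error stays at 5%.

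This model shows only the upward direction. Reversing the dependence reverses the sign.

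**4. What the recorded data could rule out.** If 60% v 40% were observed among recorded visits, setting every unrecorded visit to the least and then the most favourable value gives these limits for the 20-point difference:

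- 5% unrecorded per arm: 0.57 − (0.38 + 0.05) = +14, to (0.57 + 0.05) − 0.38 = +24 points.
- 10% per arm: +8 to +28 points.
- 20% per arm: −4 to +36 points.

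**The case against.** The strongest reply is that permission may already be sought at consent. To *remind* a patient that recording is optional implies an earlier explanation, most naturally at enrollment. The consent form is not shown and the article is a condensed account. On that reading the late reminder is a participant safeguard that any fix must keep. This largely stands. A reader might infer that patients first hear of the choice after coaching, and the text does not support that. What it does show is that the operative choice falls after allocation, and no section shows an earlier decision being taken or recorded.

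Second, the arms are more alike than they first appear. Both discuss barriers, and both take questions on the highest-priority barriers into the visit. Nothing in the article indicates that the way barriers are elicited changes willingness to be recorded. This also stands, and it means a difference by arm is possible rather than expected.

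Third, a reader might infer a bias in favour of EMPATHy. The documents give no basis for a direction. Patients who refuse because they have a sensitive barrier to raise could be more likely, not less, to reach a contextualized plan, and the illustration then turns negative.

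Fourth, it would be too strong to say that the comparison is broken beyond checking. All participants are asked to complete the baseline survey on barriers and adherence. The Encounter Form notes for each patient which questions were asked and answered and what actions were recommended. These allow a partial check, though they do not replace the audio coding, and the form is completed by a coach who knows the arm. The second primary outcome does not depend on the recording.

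Finally, the study is a pilot meant to inform a definitive trial. That lowers the stakes, but a biased pilot estimate would carry into the later design.

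**Conclusion.** The concern holds in a limited form. The patient's final choice follows the allocated coaching and is prompted by a coach who knows the arm. The physician may also decline at that stage. Unrecorded visits are removed from the first primary and first secondary outcomes. The analysed set is therefore selected after randomization and can differ by arm.

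The size is unknown because the article gives no refusal rate. With a common true rate of 40% and refusal of 20% v 10%, the false difference runs from about +4 points (refusers succeed 10% of the time) through 0 (40%) to about −3 (60%). With refusal of 5% v 3% and refusers succeeding 10% of the time, it is under 1 point. Against a design difference of 20 points, the effect could be trivial or material.

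One inference is needed: the article does not state the moment of randomization, but it must precede the arm-specific part of the coaching session and hence the reminder.

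**What to change.** - Obtain and log the patient's decision on recording at consent, and the physician's permission (standing or for that visit), before the allocation is opened.
- Keep the patient's and the physician's right to refuse or stop later, including the existing reminder.
- Report refusals before and after allocation separately, by arm. Refusals settled before allocation cannot bias the comparison among those who agreed; later ones can.
- Compare recorded with unrecorded patients by arm on the baseline survey and the Encounter Form. Section 3 of the working shows that similar refusal counts alone are not reassurance.

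The cost is small: one question fixed at an earlier point in the same appointment and one log field, with no extra visit. The main burden is asking physicians in advance; the article does not say how many there are. The gain is partial, because later reversals remain a possible arm-related loss and refusals before allocation still reduce the number analysed. The article describes enrollment as under way, so the change in timing would protect only patients not yet enrolled. Reporting by arm can cover everyone for whom the reason for a missing recording is known.

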#### Post-visit session

After the medical visit, the patients in both study conditions will meet with the coach to review the list of questions from the pre-visit coaching session. They will discuss whether the patient was able to get an answer to each of the questions and discuss the answers provided. The coach and patient will then create a plan with specific actions the patient should take in response to the answers provided by the doctor. The coach will note in the Encounter Form which questions were asked, which were answered and what action steps were recommended. The patient and coach will then set a single, simple concrete behavioral goal for the patient to complete in the subsequent 2-week period. This goal will also be noted in the Encounter Form. Finally, the patient will complete a brief post-visit questionnaire about the ease of use of the EMPATHy software (if they used it), the helpfulness of the coaching session, the relevance of the issues and concrete goals identified in the coaching session, and confidence that his or her outcomes will improve. Immediately upon completing the post-visit session, the coach will hand the participant a $20 gift card for compensation.

#### Two-week follow-up call

Two weeks after the visit, the coach will call each participant to review the concrete goal and will document in the Phone Note whether or not the patient completed the goal. They will discuss any barriers to completing the action plan and will encourage the patient to follow through. Finally, primary nonadherence will be assessed by asking whether the patient filled all prescriptions written during the study medical visit. After completing this phone call, the participant will be given a second $20 gift card for compensation.

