### Study procedures

The study protocol, delineating routine care activities (for any patient enrolled in Coached Care at the clinics) versus additional procedures unique to the study, is summarized in Figure 4. The augmented Coached Care intervention using the EMPATHy toolkit will be pilot tested in a sample of patients currently eligible to participate in the UC Irvine Health Coached Care Intervention. Two “study coaches,” in addition to the coaches providing usual care, were hired to conduct all study activities and were trained in the Coached Care intervention, use of the EMPATHy toolkit and all study procedures. Both study coaches are bilingual in English and Spanish and have a bachelor’s degree from a university. Patients enrolled in this pilot study will be randomly assigned either to complete a single coaching session using EMPATHy or to complete a single coaching session with no computer-assisted activity. Both coaches deliver both versions of the intervention. Components of the intervention visit and follow-up activities are described below.

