#### Pre-visit coaching session

All study participants will complete an intervention visit based on the routine Coached Care program in which patients are paired with a CHW coach, matched to the patient’s language and ethnicity. In both study conditions, the coach and patient will review the medical record from their most recent visit to identify one or more “red flag” issues related to their disease management such as high hemoglobin A1c, cholesterol, etc. Patients randomized to the active comparator (Coached Care with no software tools) will have an unstructured discussion of barriers to chronic disease management that may be contributing to the red flag outcome. Participants randomized to the study intervention (Coached Care + EMPATHy) will work with the coach to complete the computer-assisted activity using a tablet computer. The computer-based activity, described in more detail under “Study Intervention,” includes a brief Educational Module (EM) reviewing vignettes of barriers that many patients face, followed by a Preference Assessment (PA) module to obtain a rank ordering of the highest priority barriers that interfere with the patient’s adherence to their medication regimen and then Tailor Help (TH) to focus the rest of the visit on the highest priority barriers. In both conditions, the coach will then employ the original Coached Care protocol to help the patient generate one to three questions for the physician focusing on the highest priority barriers and will note these questions in the Encounter Form.

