**Data collection overview.**

*Primary Outcomes.* Two primary outcomes will be evaluated for this study.Development of a contextualized plan of care will be assessed by analyzing an audio recording of the medical visit using a previously developed coding scheme [35] (see “Analysis of Audio Recordings”). If the coder concludes that the plan of care discussed in the visit adequately addresses a contextual factor raised during the visit, it will be determined that a contextualized plan of care was developed.Attainment of a concrete behavioral goal will be assessed in a 2-week follow-up phone call to the patient and will be defined as the patient reporting having completed the specific action that he or she specified with the Coach as a concrete goal during the intervention post-visit.

*Secondary Outcomes:* Two secondary outcomes will be assessed.Discussion of a contextual factor in the visit will be assessed from audio recordings of the visit using a previously developed coding scheme [35]. If the coder concludes that a relevant barrier to the patient taking his or her medication consistently was raised during the visit, it will be determined that a contextual factor was discussed.Improvement in “red flag” outcomes will be assessed from the patient’s medical record as the change in the measured value of the outcome measure identified as a high priority outcome (“red flag”) from the intervention visit date till the next regularly scheduled assessment. The red flag outcome measure is selected by the Coach and patient during the intervention visit and can be either hemoglobin A1c, LDL cholesterol or blood pressure level.

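### The second primary outcome is a patient's self-report taken by a study coach who delivers both arms, with no masking of the caller described, so it is open to differential reporting or recording

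*Protocol article*

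**What the plan says.** All references are to the Protocol article.

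- **Definition.** Outcome assessments, Primary Outcomes: goal attainment is one of two primary outcomes and "will be defined as the patient reporting having completed the specific action that he or she specified with the Coach as a concrete goal".
- **Who sets the goal.** Post-visit session: "The patient and coach will then set a single, simple concrete behavioral goal for the patient to complete in the subsequent 2-week period". This comes after the allocated coaching session and the medical visit.
- **Who collects and records it.** Two-week follow-up call: "the coach will call each participant to review the concrete goal and will document in the Phone Note whether or not the patient completed" it. The same section then has the coach talk through barriers and encourage the patient, and lastly ask whether prescriptions were filled.
- **Who the coaches are.** Study procedures: two study coaches "were hired to conduct all study activities and were trained in the Coached Care intervention, use of the EMPATHy toolkit and all study procedures", and "Both coaches deliver both versions of the intervention".
- **Knowledge of the arm.** Pre-visit coaching session: an EMPATHy patient "will work with the coach to complete the computer-assisted activity using a tablet computer". The coach who ran a session therefore knows the allocation.

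The article describes no masked caller, separate assessor or verification of the reported goal. The limitations in the Discussion mention the lack of objective adherence measurement but not coach-collected self-report of a primary outcome.

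**The concern.** Treatment delivery, goal setting and outcome recording all sit in one role, held by two people. A patient asked by a coach whether the agreed goal was met may want to please. A caller who knows the arm may, without intending to, probe less or accept a vague answer more readily from a patient who used the new tool. If this happens equally in both arms, the cost is mainly power. If it happens more in one arm, it creates a difference that the planned logistic regression cannot tell from a treatment effect.

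The other primary outcome does not rest on the coach's record: it is coded from audio by two coders, with disagreements resolved by the lead researcher. Goal attainment has no comparable check. The study is powered on its primary outcomes and is meant to supply parameters for a definitive trial, so a distorted difference could carry over into that design.

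**Working it through.** **Inputs from Sample size:** 95 per group, comparator rate 40%, EMPATHy rate 60%, 80% power, alpha 0.05. Sidedness is not stated; two-sided is assumed. The article gives no misreporting rate, so every such rate below is an assumption.

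**The plan's own figure.** With unpooled variance, n per arm = (1.960 + 0.842)² × (0.40×0.60 + 0.60×0.40) / 0.20² = 94.2, which rounds up to 95. The pooled formula gives 97 per arm, and power at 95 per arm is 79.2%. The stated 190 therefore reproduces, and the two-sided reading fits (one-sided would need 77 per arm).

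**Over-reporting in the EMPATHy arm only.** Let the true rate be 40% in both arms, and let a fraction m of EMPATHy non-completers be recorded as completers. There are 0.60 × 95 = 57 non-completers per arm. Then:

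- p₁ = 0.40, p₂ = 0.40 + 0.60m, d = p₂ − p₁, p̄ = (p₁ + p₂)/2
- SE₀ = √[2p̄(1 − p̄)/95], SE₁ = √{[p₁(1 − p₁) + p₂(1 − p₂)]/95}
- P(reject) = Φ[(d − 1.96·SE₀)/SE₁] + Φ[(−d − 1.96·SE₀)/SE₁]

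For m = 0.10: p₂ = 0.46, SE₀ = √(0.4902/95) = 0.0718 and SE₁ = √(0.4884/95) = 0.0717. The first term is Φ[(0.06 − 0.1408)/0.0717] = 0.130, the second is 0.003, and the sum is 0.13.

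| Assumed m, EMPATHy only | Patients affected (m × 57) | Recorded rates | P(false significant result) |
|---|---|---|---|
| 0% | 0 | 40% v 40% | 5.0% |
| 5% | about 3 | 43% v 40% | 7.0% |
| 10% | about 6 | 46% v 40% | 13% |
| 15% | about 9 | 49% v 40% | 24% |
| 20% | about 11 | 52% v 40% | 38% |

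**Over-reporting in both arms.** What matters is the gap between the arms:

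- 10% in each arm (46% v 46%): 5.0%.
- 10% in the comparator, 15% in EMPATHy (46% v 49%): 7.0%.
- 10% in the comparator, 20% in EMPATHy (46% v 52%): 13%.

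Equal over-reporting is not free. For a true 40% v 60%, power falls from 79% to 71% when 10% of non-completers in each arm over-report (46% v 64%), and to 62% when 20% do (52% v 68%).

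**The case against.** The case against is substantial, and several stronger readings that a reader might infer do not stand.

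- **That the coach judges completion.** The outcome is the patient's report on one simple goal, and the coach writes it down. No judgement step is described, so the recorder's discretion is limited.
- **That the same coach is known to call.** The article says only that the coach calls, and there are two. Same-person calling, and with it the caller's knowledge of the arm, is a reasonable inference but is not stated.
- **That encouragement contaminates the answer.** The article lists documenting the goal before discussing barriers and encouraging. The order is not laid down as a rule, but the text does not show the reverse. Only the prescription-fill question is listed after the encouragement.
- **That differential bias is shown, or that 38% is its likely effect.** The coaches, post-visit session, call and definition are the same in both arms. The comparator is also coached, so the wish to please exists there too. The larger figures need a gap between arms of 15 to 20 percentage points in over-reporting among non-completers, for which the article gives no basis. A fair range starts at 5%.

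It is also fair to say that this is a pilot, that the other primary outcome is independent of the coach's record, and that a condensed article may leave a call script to the full protocol. What remains is a stated assignment: the article gives the recording of a primary outcome to the staff role that delivers both arms. Identical procedures do not prevent differential recording by someone who knows the arm.

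**Conclusion.** The point holds as a risk, not as a demonstrated bias. A primary outcome is an unverified self-report, collected and recorded by one of the two coaches who deliver both interventions and set the goals, and no masking of the caller is described. The size cannot be taken from the article. Under the stated assumptions (true rate 40% in both arms, 95 per arm, two-sided 0.05), the false-positive rate runs from 5% with equal over-reporting to 38% when 20% of EMPATHy non-completers alone are recorded as completers. A gap of 10 percentage points, about six patients, gives 13%. This should be fixed because the improvement is cheap and analysis cannot undo arm-dependent recording. It does not by itself invalidate the trial.

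**What to change.** Amend the Two-week follow-up call section as follows:

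1. Each study coach phones the participants coached by the other.
2. The call opens from a sheet that shows the goal text and no allocation.
3. A scripted yes/no question on completing the goal, then the prescription-fill question, are asked and recorded first.
4. The caller then notes whether the arm became known.
5. Only after that does the caller open the action plan, discuss barriers and give encouragement.

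Trial status says that enrolment and follow-up are under way. Flag calls made before and after the change, and report a sensitivity analysis by call method.

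**Cost.** A script and a call sheet, with no extra staff or calls. A less familiar caller may lose some response, and the trial will contain two ascertainment methods.

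**What it does not solve.** Patients know whether they used the software and may reveal it. Goals are still set by an unmasked coach after the allocated session, so their difficulty could differ by arm. The caller is still one of the two coaches who deliver both arms. Patient unmasking and unmasked goal setting in particular should be stated as limitations.
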